## 2 Methods and analysis

### 2.1 Study design and context

This will be a cross-sectional, descriptive, observational study in which we will analyse vascular structure, function and ageing and biomarkers of endothelial damage, and their relationship with lifestyles and psychological and inflammatory factors in adults with persistent COVID. The discussion groups will investigate the opinions and experiences of what the affectation by persistent COVID posed to these patients. The Persistent COVID study (GRS 2501/B/22) was registered in ClinicalTrials.gov (registration number: NCT05819840) in April 2023. In order to know if the subjects with persistent Covid have the parameters of structure, of vascular function, as well as the degree of altered vascular aging, we will use as a reference group, the values of these parameters available in the results of the EVA Study in the general population without previous cardiovascular disease (Gómez-Sánchez et al., 2020a), and we will also compare the results with other reference populations (Determinants of pulse wave velocity, 2010; Engelen et al., 2013; Herbert et al., 2014; Cunha et al., 2015). The study will be developed in the Primary Care Research Unit of Salamanca (APISAL) during the year 2023. In this period, we will select the sample and gather the data through questionnaires and explorations, which are described below. This project was approved by the ‘Ethics Committee of Research with Medicines of the health area of Salamanca’ on 27/06/2022 (CEIm reference code: Ref. PI 2022 06 1048). The SPIRIT verification list (Standard Protocol Items: Recommendations for Interventional Trials) (Chan et al., 2013) is available for this protocol (Supplementary Material S1).

### 2.2 Study population

Through consecutive sampling, we will select 300 subjects who meet the clinical definition of persistent COVID of the WHO, established by international Delphi consensus, along with patients, their representatives, and experts from the five continents. Persistent COVID is the condition that occurs in individuals with a history of probable or confirmed SARS-CoV-2 infection, generally three months after the onset of the disease, with symptoms that last for at least two months and cannot be explained by an alternative diagnosis. The common symptoms include, among others, fatigue, difficulty in breathing and cognitive dysfunction, and they generally have an impact on daily functioning. They can be de novo after the initial recovery from an acute episode of COVID-19 or persist from the initial disease, and they can also fluctuate or relapse over time (Soriano et al., 2022). The exclusion criteria of the study will be: terminal subjects, subjects who cannot go to the health centres, subjects with a history of cardiovascular disease (ischemic heart disease or cerebrovascular disease) and glomerular filtration rate below 30%. The individuals will be recruited from the registries of the Primary Care offices and the Persistent COVID Office of Internal Medicine in the health area of Salamanca. The sample size was calculated using the GRANMO free software (http://www.imim.cat/ofertadeserveis/software-public/granmo/), detecting a difference in cf-PWV of 0.35 metres/second between subjects with persistent COVID and a sample of Spanish population without cardiovascular disease (Gómez-Sánchez et al., 2020a). Accepting an alpha risk of 0.05 and a beta risk below 0.2 in a bilateral contrast, and assuming a standard deviation of 2.1, a total of 283 individuals are required to detect the indicated difference as significant. Therefore, the 300 subjects that will be included in the study will be sufficient. The subjects included in the study are shown in Figure 1. The patients did not participate in the design of the study; however, they will participate actively in the recruitment, by disseminating the objectives of the study and the inclusion criteria through their organisations. By means of discussion groups, we will investigate the opinions and experiences of the study population about the influence of persistent COVID on vascular health. Similarly, their opinions and attitudes will be considered to facilitate the transfer to the clinical practice. At the end of the study, we will send a detailed report to each patient with the results of the tests conducted. Moreover, a dissemination session will be organised for all the patients included in the study.

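### The 283 is a one-sample size that takes the reference mean as error-free, although the contrast is stated against a sample; 300 patients give 80% power only if that sample has about 4,860 people or more

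*Protocol article*

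**What the plan says.** Section 2.2 (Study population) gives the only sample-size calculation in the article. The target is a cfPWV difference of 0.35 m/s "between subjects with persistent COVID and a sample of Spanish population without cardiovascular disease". The error rates are set by "Accepting an alpha risk of 0.05 and a beta risk below 0.2 in a bilateral contrast", and the spread by "assuming a standard deviation of 2.1". From these inputs it reports that "a total of 283 individuals are required to detect the indicated difference as significant" and concludes: "Therefore, the 300 subjects that will be included in the study will be sufficient". It does not say whether a one-sample or a two-sample formula was used, and the size of the reference sample appears nowhere in the article.

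Three other places bear on the comparison:

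- The Introduction states the starting hypothesis as a difference between people with persistent COVID and the general population without that diagnosis. It also says that the reference values for Spanish adults come from the sponsor's own research group.
- Section 2.1 takes the published EVA Study values as the reference group and adds comparisons with other reference populations.
- Section 2.4 plans Z scores for comparison with other reference populations. For comparisons between groups it lists t or Mann-Whitney tests for two categories, ANOVA or Kruskal-Wallis, ANCOVA and regression. It names no one-sample test.

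**The concern.** A mean estimated from a sample has a standard error. If the patients are compared with such a mean, the variance of the difference has two parts: one from the patients and one from the reference. The figure of 283 contains only the first.

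The starting hypothesis concerns a population, and the sufficiency of 300 rests on this calculation alone. If the reference sample is of moderate size, the real chance of detecting 0.35 m/s is below the stated 80%. A non-significant result would then be read as stronger evidence against a difference than it is.

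**Working it through.** **Inputs (section 2.2).** Difference 0.35 m/s; SD 2.1; alpha 0.05 two-sided, z = 1.960; power 80%, z = 0.842; 300 patients. The article gives one SD, so I use it for both groups. The reference size m is not in the article and is varied as an assumption.

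**Step 1: reproduce 283.** One-sample normal formula:

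n = (1.960 + 0.842)² × (2.1/0.35)² = 7.849 × 36 = 282.6, rounded up to 283.

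This matches exactly. Other formulas with the same inputs do not: one-sample t gives 285, one-sided one-sample 223, and two-sample with equal groups 566 per group (1,132 in total). A two-sample calculation would return 283 per group only with an SD of about 1.49, or 283 in total only with an SD of about 1.05. The arithmetic is therefore right for one sample, and that is the formula behind the figure. On that basis power is 80.1% at 283 and 82.3% at 300.

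**Step 2: add the reference sample's error.**

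SE = 2.1 × √(1/300 + 1/m)

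Power = Φ(0.35/SE − 1.960)

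Difference detectable at 80% power = (1.960 + 0.842) × SE

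| Assumed reference size m | SE (m/s) | Power for 0.35 m/s | Detectable at 80% (m/s) |
|---|---|---|---|
| 300 | 0.171 | 53% | 0.48 |
| 500 | 0.153 | 63% | 0.43 |
| 1,000 | 0.138 | 72% | 0.39 |
| 2,000 | 0.130 | 77% | 0.36 |
| 4,000 | 0.126 | 79.5% | 0.35 |
| 5,000 | 0.125 | 80.1% | 0.35 |

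**Step 3: the reference size at which 300 patients suffice.** Setting power to 80% gives 1/300 + 1/m = 1/282.56, so m = 1/(1/282.56 − 1/300), or about 4,860. The same equation with 283 patients gives m of about 181,600. In practice 283 is enough only when the reference mean is taken as exact.

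**The case against.** The strongest reply is that a fixed norm was intended. The study recruits no controls, section 2.1 speaks of published reference values, and section 2.4 plans Z scores. Comparing patients with a published norm is a recognised one-sample design; under it 283 is correct and 300 patients give 82% power. This reading is open, but it does not settle the matter. Section 2.2 words the contrast as against a sample, the hypothesis concerns the general population, and a Z score built on an estimated mean and SD still carries their error. If a fixed norm is meant, that assumption has to be stated, and the conclusion narrows to a difference from the published mean.

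A second reply is that the shortfall cannot be shown without the reference size. That stands. A reader might infer that 300 patients definitely fail to deliver 80% power. The article does not support so flat a statement: it is true below about 4,860 reference subjects at equal SD and false above. Nor is the equal-groups figure of 566 the benchmark, because the comparator is an existing external dataset.

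A third reply is that adjustment may recover power. The Introduction says stiffness depends mainly on age, sex and arterial pressure, and section 2.4 plans ANCOVA. If individual reference data are available and covariates are roughly balanced (both assumptions), 300 patients regain 80% power at a residual SD of 0.35/(2.802 × √(1/300 + 1/500)) = 1.71 with m = 500, or 1.90 with m = 1,000. Against 2.1 these need about 34% and 18% of the variance explained. That is possible, but the calculation as written uses 2.1.

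A reader might also infer an inflated type I error. With m = 500 and a test against a fixed mean, the SE would be understated by √(1 + 300/500) = 1.265, and the true two-sided error for the population hypothesis would be about 12%. This is hypothetical: the article commits to no such test, and a two-group test on the reference data would carry the error.

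**Conclusion.** The point holds in conditional form. The sample-size figure is a correct one-sample number applied to a contrast worded as patients against a sample, so the reference sample's error is set to zero without saying so. With that error included and a common SD of 2.1, the claim that 300 are sufficient needs a reference of about 4,860 people or more. For assumed references of 300 to 2,000, power for 0.35 m/s is about 53% to 77%. The actual value depends on the reference size, which the article does not give, and on whether the comparison uses a smaller adjusted SD. The study's within-patient objectives are not touched. What needs correcting is the stated basis for the external comparison.

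**What to change.** Keep n = 300. In section 2.2:

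- Replace the calculation with a two-sample one that uses the actual number in the EVA reference sample.
- Report the power achieved for 0.35 m/s with 300 patients and the difference detectable at 80% power. If an adjusted comparison is planned, base both on the adjusted residual SD and say where it comes from.

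In section 2.4, state that the comparison with the reference will carry the reference sample's sampling error.

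Alternatively, if the published mean is meant as a fixed norm, say so in both sections, keep 283, and limit the conclusion to a difference from that published mean.

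The cost is a recalculated figure and a few sentences. No further patients are needed, and since the reference values come from the sponsor's own group, the number should be to hand. The downside is that the stated power will probably be less favourable.

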
**FIGURE 1 F1:**
[figure not shown]
Study flowchart.

### 2.3 Variables and measurement instruments

All measurements will be carried out within a maximum period of 10 days. The three researchers who will perform the measurements will be previously trained, following a standardised protocol, and quality will be controlled by an independent researcher. Table 1 shows the tests applied during the study.

**TABLE 1 T1:** Study variables and measurement instruments.

Sociodemographic variables	
Age, sex, marital status, education level and employment	
Anthropometric variables	
Body weight, height, body mass index, waist circumference, blood pressure	
Body composition	Inbody 230® multifrequency analyzer (Biospace)
Persistent COVID variables	
Fatigue	Modified Fatigue Impact Scale (MFIS)
Sleep quality	Pittsburgh's Sleep Quality Index (PSQI)
Attention disorders	Modified Memory Failures of Everyday (MFE-30)
Dyspnea	Modified Dyspnea Scale (mMRC)
Pain	Spanish chronic pain grade scale
Quality of life	SF-36 health questionnaire
Malnutrition	Malnutrition Universal Screening Tool (MUST)
Fragility	FRAIL scale
Functional evaluation	Functional evaluation scale after COVID-19
Lifestyles	
Diet quality	Mediterranean Diet Adherence Screener (MEDAS)
	Software developed in the Evident study
Physical activity and sedentary time	Global Physical Activity Questionnaire (GPAQ)
	Marshall Sitting Questionnaire (MSQ)
	Digital pedometer (Om ron Hj-321 lay-UPS)
Smoking habits	4-item questionnaire adapted from the MONICA study (WHO)
Alcohol consumption	Questionnaire on alcohol consumption in the last 7 days
Vascular structure	
Carotid intima-media thickness (cIMT)	Sonosite Micromax ultrasound device (FUJIFILM)
Ankle brachial index (ABI)	VaSera VS-2000® device
Vascular function	
Carotid-femoral pulse wave velocity (cfPWV)	SphygmoCor device
Cardio Ankle Vascular Index (CAVI)	VaSera VS-2000® device
Brachial-ankle pulse wave velocity (baPWV)	VaSera VS-2000® device
Cardiovascular Risk	Framingham scale
Target organinjury	
Heart evaluation	ECG (General electric 5000)
Kidney evaluation	Serum creatinine, glomerular filtration rate and albumin-creatinine ratio
Retinal vasculature evaluation	Non-mydriatic retinograph (TOPCON TRC NW 200)
Psychological factors	
Symptoms of anxiety and depression	Goldberg's Anxiety and Depression Scale (GADS)
Cognitive alteration	
Cognitive function	Montreal Cognitive Assessment (MoCA) scale
Endothelial assessment and biomarkers	
Endothelial dysfunction	ICAM-1, VCAM-1, ANGIOPOI ETI N-2, ENDOTHELI N-1
Inflammation	IL-6, IL-15, TNF-ALPHA
Immunosuppression	IL-10, PD-L1
Chemotaxis	CXCL10
Interferon response	I FN-gamm a
Viral load assessment	
Use of digital PCR (dPCR) to quantify viral RNA load in plasma and nasopharyngeal swab	
Correlation with endothelial and immune dysregulation	
Assessment of disease severity	
Analysis of the oresence of SARS-CoV-2 virus reservoirs	

#### 2.3.1 Sociodemographic variables and personal and family background

At the time of inclusion in the study, information about age, sex, marital status, education level and employment will be gathered. We will also gather information about the personal history of hypertension, dyslipidemia, diabetes, hypothyroidism, other diseases and consumption of medicines before the infection and at the time of the study, as well as the consumption of medicines that were required in the acute phase of COVID-19. Furthermore, the family background regarding cardiovascular diseases will also be gathered.

#### 2.3.2 General examination

Height will be measured in cm, with the patient in inhalation, barefoot with the ankles against the wall, using a calibrated wall height rod. With a flexible measuring tape, we will measure the waist perimeter with the tape parallel to the floor, above the iliac crests, at the end of exhalation with the patient standing and in underwear, and the hip perimeter will be recorded at the point of maximum circumference passing by the greater trochanter of both femurs. Body weight and body composition will be determined using an InBody 230 monitor (InBody Co, Ltd, Seoul, South Korea), with the patient fasting for at least 2 hours, barefoot, with light clothes and empty bladder. The body mass index will be calculated as body weight (kg) divided by height squared (m^2^). Clinical arterial pressure will be measured three times, using the mean of the last two measurements, with a validated Omron M10-IT sphygmomanometer (Omron Healthcare, Kyoto, Japan). The measurements will be carried out in the dominant arm of the participant after resting in a sitting position for at least 5 minutes, using a muff of adequate size, which will be determined by measuring the circumference of the upper part of the arm and following the recommendations of the European Society of Hypertension (ESH) (Williams et al., 2018a).

#### 2.3.3 Clinical variables and comprehensive valuation of symptoms of persistent COVID

From the clinical history of the patient, we will gather the vaccination state, the number and date of COVID-19 infections she/he had, whether the diagnosis of the disease was established based on the clinical symptoms or there is confirmation with laboratory tests, and, if so, whether the diagnosis was founded on PCR or Ag test and the variant that caused the acute infection. If the sequencing of the variant is missing, it will be considered that the infection was caused by the predominant variant in the epidemiological week at the time of the infection (data provided by the Territorial Service of Public Health, Epidemiological Service of Salamanca). The symptoms of the acute phase will be recorded through anamnesis. The symptoms presented by the patient due to persistent COVID will be recorded: 1. Systemic manifestations (fatigue, lack of energy, fever); 2. Neurocognitive manifestations (memory loss, difficulty in concentrating, brain fog or confusion); 3. Respiratory/cardiovascular manifestations (dyspnea, weight loss, coughing, sore throat); 4. Musculoskeletal manifestations (muscle pain, joint pain, reduced mobility); 5. Neurological/neuromuscular manifestations (cephalea, taste or smell distorsion, lack of reflexes); and 6. Psychosocial or psychiatric manifestations (depression, anxiety, sleep alterations) (Ceban et al., 2022; Oliveira et al., 2022; Pinzon et al., 2022; Swarnakar et al., 2022; Zeng et al., 2023). We will also obtain information from the patient about the typical symptomatic fluctuation of the disease, asking her/him whether there was a period free of symptoms after the acute infection, whether the symptoms range in intensity, whether she/he presents days free of symptoms, and, if so, how many symptom-free days she/he has had in the last 30 days.

The *comprehensive health valuation* of the subjects affected by persistent COVID will be carried out using the following scales:

The *functional valuation* will be performed with the functional valuation scale after COVID-19 (Severe Acute Respiratory Syndrome, 2021). The questionnaire is divided into two parts (a and b), which will be completed independently. The response options of the two parts will be evaluated from grade 1 to grade 4 as a function of the limitations of the patient.

The *valuation of fatigue* will be conducted using the modified fatigue impact scale (MFIS) (Kos et al., 2005), which consists of 21 questions and evaluates the effects of fatigue during the last 4 weeks, based on a multidimensional approach with cognitive, physical and psychosocial components. Each question is valued from 0 to 4; the total score ranges from 0 to 68, and higher scores indicate greater fatigue.

*Sleep quality* will be evaluated with Pittsburgh’s sleep quality index (PSQI) (Royuela and Macías, 1997), which consists of 10 questions and assesses how the patient’s sleep was during the last month. The first 4 questions refer to specific data about the time the patient goes to bed, the time that it takes him/her to fall asleep, the time when he/she wakes up, and the number of hours he/she sleeps. The following 5 questions reflect more objective data about the sleep problems that the patient suffers from, and the last question is whether the patient sleeps accompanied or alone. The response options are: never in the last month; less than once per week; between once and twice per week; and three or more times per week. The total score may range between 0 and 21 points, with higher scores representing worse sleep quality.

*Attention disorders* will be evaluated using the modified memory failures of everyday (MFE-30) (Montejo et al., 2014). This questionnaire consists of a list of 30 memory failures that may happen in daily living. They are valued as: never or almost never; seldom; sometimes; often; and always or almost always.

*Dyspnea* will be assessed with the modified dyspnea scale (mMRC) (Council, 1966), in a range of 0 to 4, with higher scores indicating greater dyspnea.

*Pain* will be measured using the Spanish chronic pain grade scale (Ferrer-Pena et al., 2016). The questionnaire consists of 8 items about the presence or absence of pain in the patient, its intensity, and its impact on the realisation of activities of daily living, leisure and work in the last three months.

*Quality of life* will be evaluated with the SF-36 health questionnaire (Alonso et al., 1995), which consists of 36 items that gather aspects about physical functioning, physical role, body pain, general health, vitality, social functioning, emotional role and mental health in the last four weeks. Additionally, the SF-36 includes an item about the change in the general health state with respect to the last year.

*Malnutrition* will be assessed using the Malnutrition Universal Screening Tool (MUST) (Scott, 2008; Krznaric et al., 2020). This questionnaire evaluates the BMI, weight loss in the last 3-6 months, and the intake capacity in the last 5 days, classifying the subjects based on their scores in three categories: low risk (0 points), intermediate risk (1 point) and high risk (≥2 points).

*Fragility* will be measured with the FRAIL scale (Morley et al., 2013), which consists of 5 dichotomous questions, valued from 0 to 1, and it analyses five dimensions: fatigue, resistance, aerobic performance, comorbidity and weight loss in the last year. The score ranges from 0 to 5 points, with the following interpretation: probable fragility (3-5 points), probable pre-fragility (1-2 points), and robustness or no fragility (0 points).

#### 2.3.4 Lifestyles

##### 2.3.4.1 Diet quality

*Adherence to the Mediterranean diet* will be measured using the 14-item validated questionnaire Mediterranean Diet Adherence Screener (MEDAS) (Schröder et al., 2011), which was developed by the PREDIMED research group. Each question will be scored as 0 or 1. Adequate adherence to the Mediterranean diet will be assumed for a total score of ≥9 points. With the application developed in the EVIDENT study (Lugones-Sanchez et al., 2022) (registration number: 00/2014/2207), we will record the consumption of food throughout a regular week.

##### 2.3.4.2 Physical activity and sedentary time

*Physical activity* will be objectively evaluated with a validated digital pedometer (Omron Hj-321 lay-UPS) (Steeves et al., 2011), which measures the total steps, the aerobic steps, the distance travelled in Km and the calories burnt in the last 7 days. The participants will carry the pedometer for 9 days, in order to gather the activity performed in 7 full days. These parameters will also be subjectively measured with the global physical activity questionnaire (GPAQ) (OMS, 2014) developed by the WHO. This questionnaire gathers information about participation in physical activity and sedentary behaviour in the last 7 days during work, commuting and leisure time. The doses of physical activity will be estimated in METs/min/week, and those participants who reach 450 METs/min/week will be considered active.

*Sedentary time* will be assessed with the *Marshall Sitting Questionnaire (MSQ)* (Marshall et al., 2010). This questionnaire is validated and evaluates the sitting time in hours and minutes during weekdays and weekends in five domains: commute, work, watching TV, use of computers at home, and unspecified leisure in other domains. The total daily sedentary time will be calculated by adding the session time for each domain.

